#### Secondary outcomes

##### Patient-reported

Within 24 h after the clinic visit, we will collect the following patient-reported outcomes: the SURE measure of decisional conflict [29], the collaboRATE measure of SDM [27], a single item added to collaboRATE to assess effort to compare costs of treatment, the CAHPS measure of communication quality [28], and the COST measure of financial toxicity [31, 32]. Financial toxicity will be an exploratory outcome.

At 3-month follow-up, we will collect the following patient-reported outcomes: the SURE measure of decisional conflict [29], the decision regret scale [30], and the COST measure of financial toxicity [31, 32]. Financial toxicity will be an exploratory outcome.

##### Clinician-reported

Participating urologic surgeons will complete a 12-item measure of SDM perceptions [33] at the start of their arm assignment and again at the end of the study period. Each study urologic surgeon will also complete an adaptation of the Ottawa Acceptability Scale [34] and survey items about feasibility of routine Option Grid use at the end of the study period.

Table 2 summarizes all study measurement, including outcomes and planned covariates.

### Randomization

We will randomly allocate clusters (urologic surgeons) to the intervention sequences with a simple randomization approach (i.e., no blocking, stratification, or other constraints) using R statistical software. Randomization will take place after urologic surgeon recruitment is complete; both participating urologic surgeons and the study team are therefore blinded to allocation until after urologic surgeon recruitment. The study coordinator (KP) will enroll clusters (urologic surgeons) to the study. The study statistician ([name]), blinded to the identity of each cluster, will generate the randomization schedule and assign cluster IDs to sequences.

Eligible patients will be recruited continuously throughout the study period; the study coordinator (KP) will identify eligible patients and seek their informed consent to participate during both control and intervention periods. In order to manage logistics of implementing the intervention and recruiting patient participants, the principal investigators ([name], GE), study coordinator (KP), and participating urologic surgeons will learn the allocated sequence assignments immediately post-randomization. Patients will not be informed of their study arm allocation during the recruitment process, but will not be blinded as they will observe whether or not they receive the Option Grid intervention at the time of their visit. Other members of the study team, including those analyzing results, will remain blinded to cluster sequence allocation throughout the study.

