### Outcomes

#### Primary outcomes

We will measure the frequency of cost conversations, initiator of cost conversations, and whether or not a referral is made to address costs. We will collect these primary outcomes by patient report from all participating patients in a questionnaire completed immediately post-visit (or shortly after a telehealth visit).

We will also use an existing observer checklist [14] to assess these outcomes for participating patients who consent to audio-recording their clinic visits. We will use Hunter et al.’s approach to defining a cost discussion: “any mention of the patient’s out-of-pocket expenses or insurance coverage for a past, present, or potential health care service” [26]. For example, any mention of costs or insurance coverage for primary surgery, radiation, imaging, as well as indirect costs of care such as time off work, transportation, recovery time, will be documented and included in our analyses. If direct or indirect costs are mentioned per Hunter’s definition [26], we will indicate that costs were discussed during the consultation. If there are two mentions of cost in one transcript, with a different topic in between, the mentions will be coded as two cost discussions. If costs are discussed at all, the subsequent items (length of time of the cost conversation, number of times cost was discussed, who initiated the cost discussion, content of cost discussions, whether a referral is made to address costs) will then be evaluated. We will document references to the Option Grid to examine whether the Option Grid directly prompted the cost conversation. Because we do not expect surgeons to know specific details about treatment costs, the checklist also includes an item to measure whether a referral is made to address more detail about costs. We will document to whom a referral is made (navigator, social worker, outside resource).

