#### Data collection

##### Observational data

For participating patients who agree during the study consent process to audio-recording of their in-person clinic visits, the study coordinator will start a digital recorder when the patient enters the exam room and return to collect the recorder at the end of the clinic visit. Where participating patients agree to audio-recording of their virtual visits, audio-recordings will be captured by the urologic surgeon through Zoom or other HIPAA-compliant telemedicine software and subsequently transferred securely to the study coordinator.

Audio-recordings will be transcribed verbatim for analysis. Two members of the study team will independently review each transcript and apply the observer checklist [14, 26] to identify frequency and initiator of cost conversations and frequency of referrals to address costs.

At the time of patient enrollment, study staff will review the electronic health record to determine whether or not the participant has been diagnosed with each of the 20 most common and costly health conditions, as described in the Medical Panel Expenditure Survey [37–39], and record those comorbidities in the study’s Research Electronic Data Capture database (REDCap). At 3-month follow-up, study staff will collect the patient’s received treatment (if any) from the electronic health record and record that information in REDCap.

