### Analysis

We will perform unadjusted bivariate comparisons of outcomes and predictors across intervention groups using t tests for continuous variables and chi-square tests for categorical variables. We will also conduct analysis adjusting for patient demographic characteristics, patient clinical characteristics, and the time period when the patient began follow-up. We will use logistic regression to model the Aim 1 primary outcome of whether or not a cost conversation occurred. In Aim 2, we will use linear regression to analyze outcomes with multi-level scales (e.g., decision regret scale [30]) and logistic regression to analyze binary outcome measures (e.g., collaboRATE [41]). To account for clustering of patient participants by urologic surgeon, we will estimate hierarchical models with urologic surgeon random effects. Let *Y*_*ijt*_ denote an outcome measured on the *i*th patient of the *j*th surgeon at time *t* and *OG*_*jt*_ indicate whether surgeon *j* has transitioned from usual care to the Option Grid (OG) by time period *t*. To lessen the reliance on the random assignment of surgeons to step times to balance any changes across time between the intervention groups, we adjust for the time period when the patient began follow-up, patient demographic and patient clinical characteristics. Adjustment for time period will be enabled by including indicator variables for time periods 2 through 5 (making time period 1 the excluded category) with effects denoted by {*λ*_*t*_}=_*t* = 2 : 5_ while all other patient-level variables will be included in a vector of covariates, denoted *X*_*ijt*_. Therefore, the model for the Aim 1 analysis and those outcomes modeled as binary random variables in Aim 2 has the form
1$$ logit\left(\Pr \left({Y}_{ijt}=1\left|{\theta}_j\right.\right)\right)={\beta}_0+{\beta}_1{OG}_{jt}+{\beta}_2{X}_{ijt}+{\lambda}_t+{\theta}_j $$

while the model for those outcomes modeled as continuous variables in Aim 2 has the form
2$$ {Y}_{ijt}={\beta}_0+{\beta}_1{OG}_{jt}+{\beta}_2{X}_{ijt}+{\lambda}_t+{\theta}_j+{\varepsilon}_{ijt} $$

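### The stated blinding of the remaining study team cannot hold: the analysis data disclose each cluster's sequence, and transcripts that mention the Option Grid disclose that visit's arm to coders

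*Protocol article*

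**What the plan says.** The Randomization section sorts people into three groups.

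- **Told the allocation.** The principal investigators, the study coordinator and the surgeons: "participating urologic surgeons will learn the allocated sequence assignments immediately post-randomization".
- **Patients.** Openly described as not blinded once the visit takes place.
- **Everyone else.** "Other members of the study team, including those analyzing results, will remain blinded to cluster sequence allocation throughout the study".

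The same section gives the study statistician a narrower mask: this person, "blinded to the identity of each cluster, will generate the randomization schedule and assign cluster IDs to sequences".

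Three other sections bear on the third group.

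- **Analysis.** The models contain OG_jt, defined to "indicate whether surgeon *j* has transitioned from usual care to the Option Grid (OG) by time period" t, and indicators for periods 2 to 5.
- **Observational data.** "Audio-recordings will be transcribed verbatim for analysis", and "Two members of the study team will independently review each transcript and apply the observer checklist". The two people are not identified by role.
- **Primary outcomes.** The checklist is used to "assess these outcomes for participating patients who consent to audio-recording their clinic visits". The same description adds: "We will document references to the Option Grid to examine whether the Option Grid directly prompted the cost conversation".

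**The concern.** The article makes a positive claim of blinding and then describes procedures that defeat it. There are two separate problems.

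The first is accuracy. A reader would take it that the analysts do not know which clusters were under the intervention when, although the model cannot be fitted without that information.

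The second is outcome assessment. Frequency, initiator and referral are primary outcomes, each measured by patient report and by observation. Patients know whether they received the grid, so the observed version is the only one that masking could protect. If coders know the arm, their expectations can enter the scoring. Hypotheses 1.1 to 1.3 each predict a direction. Double coding does not remove this risk: both coders see the same cue, and agreement between them would not reveal a shared lean.

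**Working it through.** The plan gives no figure on this point to reproduce. The check sets the sections side by side, with one logical test.

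**Analysts**

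1. Inputs: four sequences, five periods and five surgeons (Design); all surgeons in usual care at the start (Intervention implementation, Option Grid training); OG_jt and period indicators in the models (Analysis).
2. Code usual care as 0 and intervention as 1. With one step per period, the sequences are 01111, 00111, 00011 and 00001. The design figure is not shown, so this layout is the standard reading of the text.
3. Suppose the analyst receives neutral arm codes. The labels hide the allocation only if swapping 0 and 1 can turn a valid sequence into another valid one. The swapped patterns are 10000, 11000, 11100 and 11110. All begin with 1, whereas every valid sequence begins with 0. Matches: 0 of 4.
4. A data set with cluster ID, period and OG therefore shows each cluster's sequence and which code is the intervention. This needs only the common start in usual care and the one-way crossover, not the exact step times. What can still be hidden is which surgeon a cluster ID stands for, the mask already described for the statistician.

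**Coders**

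1. The transcripts are verbatim, and no masking step is described.
2. Decision aids were not routine in these practices before the study (Setting), so a mention of the Option Grid points to an intervention visit.
3. References to the grid are to be recorded in the course of the observer assessment, so the plan expects them to occur.
4. The coders' roles are open, which leaves two cases. If they are among those told the allocation, the Randomization sentence is not contradicted, but they are not masked. If they are other team members, they learn the arm of every visit whose transcript mentions the grid. In neither case are such visits scored masked.
5. A transcript without a mention does not reveal its arm through this cue.

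**Which items are exposed**

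- Occurrence: one mention of out-of-pocket expense or insurance coverage is enough, which leaves little discretion. The Analysis section models occurrence as yes or no, so the rule for splitting separated mentions affects the count and not that model.
- Initiator: someone must judge who began the talk when a cost row of the grid prompted it.
- Referral: the grid itself lists a social-work contact and a support website (Table 1), so someone must judge whether pointing to that list is a referral.

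**The case against.** The case on the other side is substantial.

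- The Randomization sentence concerns cluster sequence, not the arm of a single visit, and neither section on the observed outcomes calls the coding blinded.
- The article does not say who logs Option Grid references, when, or whether this is a checklist item.
- The grid reaches patients before the visit by web link, post or portal (Option Grid delivery), so an intervention visit may never name it.
- Only recorded visits are involved. The patient-reported versions of the same outcomes cover all participants and cannot be touched by coder bias.
- De-identification and coding order are details that a condensed article may leave to a coding manual.

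Most of this stands, and it limits the point. It does not rescue the sentence for analysts, and it does not remove the cue from transcripts that mention the grid. The criticism is not that a coding manual is absent; it is that a stated property conflicts with stated procedures.

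Two stronger readings are tempting.

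- A reader might infer that the observed primary outcomes are scored by unblinded coders because the analysts hold OG_jt. That does not follow: the analysts' data say nothing about the coders, who are nowhere said to be given the allocation and can learn it only visit by visit.
- A reader might put a size on the bias. With no true effect, the plan's 33.3% usual-care rate, and an assumed 10% or 20% of cost-free intervention visits scored as cost talk, the spurious difference is 0.10 × (1 − 0.333) = 6.7 points or 0.20 × (1 − 0.333) = 13.3 points. Against the planned difference of about 33 points, that is 20% or 40%. The arithmetic is right, but the documents support neither rate, the direction is assumed, and the sum covers only occurrence, the item with least discretion.

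**Conclusion.** The blinding claim is wrong as written for analysts. This follows from the design and the model, and rests only on the common start in usual care and the one-way crossover. They can be masked to surgeon identity and to nothing more.

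For coders the conclusion is narrower. In the audio-recorded subset, masking fails at any visit whose transcript mentions the grid, and the article describes no safeguard. It is likely, but not stated, that the people who score the cost items also log the grid references. The resulting room for bias lies mainly in initiator and referral. Its size and direction are unknown, and the share of recorded visits that mention the grid is not given. The point deserves correction because the remedy is cheap, not because bias has been shown.

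**What to change.** 1. Rewrite the blinding statement in Randomization to say, for each role, what is masked: surgeon identity, sequence or visit arm. Drop the claim that analysts are blinded to sequence.
2. Use coders who do not hold the allocation. Give them transcripts in random order with surgeon, date and period removed. Replace every reference to written or online material with the same token in both arms; a token used for the Option Grid alone would itself signal the arm.
3. Have them score and lock occurrence, initiator and referral on these transcripts. Only then release the unmasked transcript for coding Option Grid references and whether the grid prompted the talk.
4. Report coder masking as partial.

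The cost is some clerical time in preparing transcripts and a short second pass. Masking will be imperfect, because the cost content has to stay in and indirect allusions to the grid may be missed.

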### Procedures

Figure 2 summarizes study enrollment, interventions, and assessments.

**Fig. 2 Fig2:**
[figure not shown]
Schedule of enrollment, interventions, and assessments

#### Stakeholder advisory group

A stakeholder advisory group comprising patients, clinicians, and prostate cancer advocates has informed our study design, outcomes, and procedures. This group will meet every 1 to 2 months throughout the study period to co-design study materials, monitor study progress, and troubleshoot problems where necessary. We compensate these stakeholder partners at a rate that reflects their substantial expertise and commitment.

#### Recruitment

##### Clinician recruitment

Urologic surgeons who wish to participate will register their interest with the urology division chief, who will share their contact details with the principal investigator ([name]) to facilitate enrollment. In the weeks prior to the start of the study period, the study coordinator (KP) will seek written informed consent from interested and eligible urologic surgeons by phone and/or email.

##### Patient recruitment

We will recruit patient participants from July 2020 through September 2021. The study coordinator will identify potentially eligible patients with upcoming clinic visits using clinic schedules, electronic health records, contact with clinicians, and contact with clinic coordinators, then confirm eligibility with the patient’s urologic surgeon. The study coordinator will retrieve phone numbers for eligible patients from the electronic health record. To assess interest in participating, the study coordinator will contact each eligible patient by phone before their scheduled visit, but after the care team has communicated a prostate cancer diagnosis to the patient. To reduce risk of selection bias due to unblinded treatment allocation, the study coordinator will approach all eligible patients, defined as men with prostate cancer who have a Gleason 6 or 7 and/or PSA less than or equal to 10 ng/ml, or as referred by a surgeon whose clinical expertise confirms that the individual is eligible for the options in the Option Grid intervention. If the eligible patient is interested in participating, the study coordinator will document informed consent over the phone, electronically as a waiver of written consent for those who agree to be emailed, or in-person when the patient arrives for the clinic visit.

#### Data collection

##### Observational data

For participating patients who agree during the study consent process to audio-recording of their in-person clinic visits, the study coordinator will start a digital recorder when the patient enters the exam room and return to collect the recorder at the end of the clinic visit. Where participating patients agree to audio-recording of their virtual visits, audio-recordings will be captured by the urologic surgeon through Zoom or other HIPAA-compliant telemedicine software and subsequently transferred securely to the study coordinator.

Audio-recordings will be transcribed verbatim for analysis. Two members of the study team will independently review each transcript and apply the observer checklist [14, 26] to identify frequency and initiator of cost conversations and frequency of referrals to address costs.

At the time of patient enrollment, study staff will review the electronic health record to determine whether or not the participant has been diagnosed with each of the 20 most common and costly health conditions, as described in the Medical Panel Expenditure Survey [37–39], and record those comorbidities in the study’s Research Electronic Data Capture database (REDCap). At 3-month follow-up, study staff will collect the patient’s received treatment (if any) from the electronic health record and record that information in REDCap.

##### Patient-reported data

We will administer post-visit patient questionnaires at two timepoints: immediately after the clinic visit and 3 months after the clinic visit. At both timepoints, study staff will collect patient-reported data by emailed link to an online survey form hosted in REDCap or by standardized telephone interview, depending on participant preference. All questionnaire data will be stored in REDCap and response modality will be recorded. Study staff will make up to five attempts to contact patient participants for response to each survey.

After completion of the first post-visit questionnaire, study staff will mail patient participants a $15 gift card. After completion of the second questionnaire at 3-month follow-up, study staff will mail patient participants a $5 gift card.

##### Clinician-reported data

For each set of clinician-reported outcomes, the study coordinator will email a link to an online survey hosted in REDCap to each participating urologic surgeon. The study team will send email reminders as needed until responses are collected from each participating urologic surgeon. Upon completion of all study procedures, the study team will provide a $50 gift card to each participating urologic surgeon at the end of the study period.

#### Intervention implementation

##### Option Grid training

At the start of the study period, while all urologic surgeons are allocated to the usual care control condition, study staff will schedule an Option Grid training session with each urologic surgeon to be held at the beginning of his or her designated intervention period. Training sessions will be led by the principal investigators ([name] and GE) and held in-person and/or by Zoom videoconference.

##### Option Grid delivery

Participating urologic surgeons will deliver the Option Grid to all their patients who face a management decision for slow-growing prostate cancer. Some urologic surgeons will direct patients to access the Option Grid through a secure web link prior to their visits, while others will send the Option Grid to patients by postal mail or through the online patient portal. At the time of patient enrollment, the study coordinator will confirm that each participating patient has received the Option Grid from their care team. If a participating patient has not received the Option Grid, study staff will provide it by email or postal mail prior to the patient’s visit.

### Sample size

We assume given the study timeline and projected patient volumes that it is feasible to recruit up to 50 patients from each of the five participating urologic surgeons, to target a total of 200 patient participants. Due to the novelty of our shared decision-making intervention intended to promote cost conversations in cancer care, limited data were available to inform the assumed ICC [14]. Based on the unmeasured clinician-level variability observed in other studies using similar interventions to study different outcomes, we conservatively assumed a relatively large ICC value of 0.05. Under these assumptions, and assuming an intraclass correlation coefficient of 0.05 for our primary outcome, the design effect of the stepped-wedge design equals 3.12, making the effective sample 32 per intervention group; this is the equivalent sample-size under a design in which there is no clustering of patients within surgeons [40].

In relation to Aim 1 and our primary research questions, prior research demonstrates that surgeons who used an encounter decision aid about early-stage breast cancer surgery with comparative cost information were far more likely to engage in cost conversations compared to those using a decision aid without cost information or those in usual care (66.7% versus 33.3%) [14]. Surgeons in the cost information decision aid group were also more likely to initiate these conversations compared to those in the non-cost information decision aid group (86.4% versus 34.1%) [14]. We estimated power directly for a stepped-wedge design. A requirement for performing this calculation is supplying the between-cluster variance. We estimated this quantity by solving for its value given the specified ICC of 0.05 and the within-cluster variance of a Bernoulli (binary-valued) random variable, whose mean equals the average value of the assumed probabilities of the outcomes for the two comparison groups (0.5, the most conservative value we could assume). The resulting power for a two-sided test was estimated to be 0.804. A projected sample size of 200 is therefore sufficient to answer our primary research questions.

Our two-step approach to the included sample size calculation involved mathematical approximations, which may reduce its reliability. While the alternate method of calculating power using a simulation model may have improved the reliability of our sample size calculation in some ways, that approach would require additional assumptions about the effects of time and other covariates on the basis of little available empirical evidence, which may also reduce overall reliability. Therefore, we favor the simpler calculation.

Because of the low-risk nature of the intervention with regard to likelihood and magnitude of potential harms, we do not plan to conduct interim analyses and have not established stopping guidelines.

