## Methods

### Design

This study uses a stepped-wedge cluster-randomized trial design (see Fig. 1) [19]. There are four sequences, with at least one cluster (urologic surgeon) randomized to each sequence. The fifth urologic surgeon will be assigned to the second sequence in order to balance patient accrual to the intervention and control arms. There are five periods, each lasting 3 months, for a total study duration of approximately 15 months. Independent eligible patients will be enrolled at each period within a cluster (urologic surgeon).

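### The stated power of 0.804 does not follow from the five-surgeon, 200-patient design: the protocol's own recipe gives about 0.78 with equal accrual, and the design effect of 3.12 is not reproduced either

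*Protocol article*

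**What the plan says.** The Design section has four sequences and five periods, with at least one surgeon randomized to each sequence. "The fifth urologic surgeon will be assigned to the second sequence", so the five surgeons cross over after periods 1, 2, 2, 3 and 4.

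The Sample size section considers it "feasible to recruit up to 50 patients from each of the five participating urologic surgeons, to target a total of 200 patient participants". On the ICC it says "we conservatively assumed a relatively large ICC value of 0.05". It then reports that "the design effect of the stepped-wedge design equals 3.12, making the effective sample 32 per intervention group".

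Power is said to have been computed directly for a stepped wedge. The between-surgeon variance was obtained by "solving for its value given the specified ICC of 0.05 and the within-cluster variance of a Bernoulli (binary-valued) random variable", with the mean set at the average of the two assumed rates ("0.5, the most conservative value we could assume"). The rates are 66.7% and 33.3%. The result is given as "The resulting power for a two-sided test was estimated to be 0.804", and from this the section concludes that 200 patients suffice.

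The section does not state how many surgeons, how many patients per surgeon-period, or which alpha went into that figure.

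**The concern.** The conclusion that 200 patients suffice rests on a power only just above the customary 0.80. The recipe is explicit enough to be rerun. If the printed figure belongs to a different layout from the one in the Design section, the sufficiency statement is not supported as written.

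The section also gives a second summary, a design effect of 3.12 and 32 effective patients per group. A reader would expect it to describe the same design as the power figure. If the two cannot be obtained from one layout, the reader cannot tell what was calculated.

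**Working it through.** **Inputs.**
- From Sample size: within-surgeon variance 0.5 × 0.5 = 0.25; ICC 0.05; difference 0.667 − 0.333 = 0.334; N = 200.
- From Design: four sequences, five periods, fifth surgeon in sequence 2.
- From Analysis: period indicators and a surgeon random intercept.
- Assumed: two-sided alpha 0.05 and, for the main case, equal accrual over surgeons and periods.

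**Formulas (Hussey–Hughes).** Between-surgeon variance τ² = 0.25 × 0.05 / 0.95 = 0.01316. With n patients per surgeon-period, σ² = 0.25 / n. For I surgeons and T = 5 periods,

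Var = I σ² (σ² + T τ²) / [(I U − W) σ² + (U² + I T U − T W − I V) τ²],

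where U is the number of intervention surgeon-periods, W is the sum over periods of the squared number of surgeons on intervention, and V is the sum over surgeons of the squared number of intervention periods. Power = Φ(0.334 / √Var − 1.960).

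**Step 1: reproduce the printed figure.** Four surgeons, one per sequence, 50 patients each, so n = 10 and σ² = 0.025. U = 10, W = 30, V = 30.
- Numerator: 4 × 0.025 × 0.09079 = 0.009079.
- Denominator: 10 × 0.025 + 30 × 0.01316 = 0.6447.
- Var = 0.01408, SE = 0.1187, power = Φ(2.815 − 1.960) = 0.8036, which rounds to 0.804.

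**Step 2: the design as described, equal accrual.** Five surgeons, 40 patients each, so n = 8 and σ² = 0.03125. U = 13, W = 51, V = 39.
- Numerator: 5 × 0.03125 × 0.09704 = 0.01516.
- Denominator: 14 × 0.03125 + 44 × 0.01316 = 1.0164.
- Var = 0.01492, SE = 0.1221, power = Φ(2.735 − 1.960) = 0.781.

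**Step 3: how far this depends on assumptions.**
- *Five surgeons at 50 each (N = 250):* power 0.856, so this layout does not give 0.804 either.
- *0.25 read as total variance* (within 0.2375, between 0.0125): 0.801 for five surgeons × 40 and 0.823 for four × 50.
- *Unequal splits of 200 over five surgeons, none above 50, literal recipe:* roughly 0.73 to 0.805, with a median of about 0.78 over random splits. The top value arises when the two sequence-2 surgeons share 50 patients and the others recruit 50 each. With 50 each in sequences 1 and 2 (both surgeons) and 25 each in sequences 3 and 4, power is 0.734. The range is not a strict bound: if the sequence-4 surgeon recruits almost nobody, power is 0.642.
- *Patients needed for 0.80 with equal splits:* 210 give 0.798 and 215 give 0.806.

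**Step 4: the design effect.** I divide Var by the variance of an unclustered, equal-arm comparison, 4v / N. The divisor depends on whether v is the within-surgeon variance (0.25) or the total variance (0.25 / 0.95 = 0.263).

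| Layout | Var | Design effect, v = 0.25 | Design effect, v = 0.263 |
|---|---|---|---|
| 4 surgeons × 50 | 0.01408 | 2.82 | 2.68 |
| 5 surgeons × 40 | 0.01492 | 2.98 | 2.83 |
| 5 surgeons × 50 | 0.01222 | 3.05 | 2.90 |

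No entry is 3.12. The step from 3.12 to 32 is sound: 200 / 3.12 / 2 = 32.05.

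**Step 5: does 32 per group support 0.804?** A two-group comparison with 32 per group gives 0.762 with variance 0.25 in each group, 0.775 with the usual pooled test and 0.809 with unpooled variances. It does not settle the matter.

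**The case against.** **The four-surgeon origin is an inference.** A reader might take the match in Step 1 as proof that the fifth surgeon was omitted. The article does not say how many clusters were used, and one agreement to three decimals is suggestive only. This objection stands.

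**Equal accrual is my input.** The protocol states no split. The literal recipe reaches 0.805 with five surgeons and 200 patients if the two sequence-2 surgeons together recruit 50. It would therefore be too strong to say that the described design cannot reach 0.80. This stands too, but the favourable split is one the protocol does not plan.

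**Five times 50 is 250, not 200.** A reader might call this a plain contradiction. It is not: the wording sets a ceiling per surgeon, and five surgeons at or below it can total 200. The wording only leaves open which layout was used.

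**Variance convention.** Reading 0.25 as total variance gives 0.801 for five surgeons × 40. But the text says within-cluster, 0.801 is still not the printed value, and the same reading gives 0.823 for four × 50. This shows that the gap is small, not that the figure is right.

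**Disclosed approximation, and a separate design effect.** The section concedes that its two-step method is approximate. That passage weighs an analytic calculation against simulation and does not cover the choice of layout. Because power was computed directly, 3.12 need not feed into 0.804, and it rests on a cited method that is not shown. I therefore say only that it is not reproduced under the same model.

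**Non-response and small-sample tests.** One could add losses to the survey or a t reference for five clusters. The document gives no response rate, and a condensed article may leave such detail to the full protocol or analysis plan. I draw nothing from either.

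**Conclusion.** The point holds. Under the recipe as written, five surgeons in sequences 1, 2, 2, 3 and 4 with 200 patients split equally have power of about 0.78, not 0.804, a difference of about 2.3 percentage points. This rests on alpha 0.05, equal accrual, variance 0.25 within surgeons and the normal approximation. The printed value coincides with four surgeons × 50, which suggests its origin but does not establish it.

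The design effect of 3.12 lies above the 2.68 to 3.05 obtained from the three layouts under either variance convention, so the section's two summary figures are not obtained from any one of these layouts.

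Severity is minor to moderate. A reader might infer that the trial is seriously underpowered or that its target must rise. The documents do not support that: power stays close to 0.80, some accrual patterns reach it, and neither the design nor the analysis is affected. What fails is the statement that 0.804 is the power of this design and that 200 is sufficient on that ground.

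**What to change.** In the Sample size section:
1. State the number of surgeons, their sequences, the patients per surgeon-period and the alpha behind the power figure.
2. Restate power as about 0.78 for five surgeons and 200 patients with equal accrual (about 40 per surgeon, 8 per surgeon-period), and word the sufficiency conclusion to match. If another split was intended, state it and give the power for that split.
3. Recompute the design effect and effective sample for the same layout and name the variance convention. For five × 40 they are 2.98 and 100 / 2.98 = 33.5 per group on variance 0.25, or 2.83 and 100 / 2.83 = 35.3 on total variance. Otherwise delete both figures, since the power calculation does not need them.
4. Describe 50 per surgeon as a ceiling and 40 as the expected average.

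The cost is a rewording of one section and a slightly less favourable stated power. No extra patients and no change to the design or analysis are required.
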